### Participant timeline

In-patients and out-patients will regularly be screened for participation eligibility. If the eligibility criteria are met and in consultation with their treating clinicians, patients will be informed about their study and will have at least one day to consider participation and sign the informed consent. The same procedure applies for clinicians who participate in the study, while they only must consent once for the recording of therapy sessions with several patients who gave informed consent. From the time point on where patients agreed to participate, up to five of their regularly held therapy sessions will be recorded. After the therapy session, patients and therapists will fill out questionnaires about the psychopathology of the patient (approx. 5 min. for each). They are asked to fill out the questionnaire on the same day the therapy session took place. Table 1 summarizes the procedure and when the respective questionnaires are used.

**Table 1 T1:** Content for the schedule of enrollment and participation.

TIMEPOINT	Enrollment	Informed Consent	Recording and Questionnaires				
	*−t2*	*−t1*	*t1*	*t2*	*t3*	*t4*	*t5*
	Ongoing	After confirmation by clinician	At least 1 week between each participation				
			Up to five therapy sessions can be recorded per participant				
			Questionnaires have to be filled out the same day as the recording				
*Study admission*							
Eligibility screen	X	X					
Consultation with the treating clinician	X						
Informed consent		X					
*Recording of therapy session*			X	X	X	X	X
*Patient reported outcomes (PRO)*							
*Beck’s Depression Inventory (BDI-II)*			X	X	X	X	X
*DSI-SS-Scale*			X	X	X	X	X
MINI C Suicidality Scale			X				
*Demographics, Diagnoses and Concomitant Medication*			X				
*Therapist Ratings*							
*Global Assessment of Functioning (GAF)*			X	X	X	X	X
*Clinical Global Impression (CGI)*			X	X	X	X	X
*Brief Psychiatric Rating Scale (BPRS)*			X	X	X	X	X

### Sample size

To determine the required sample size for comparing the accuracy of our models against the gold standard of a trained psychiatrist's evaluation, we conducted an *a priori* power analysis using G*Power software (43).

We based our effect size estimate on the accuracies reported in previous studies that used machine learning techniques to predict suicidality from clinical data (44). Pestian et al. (45) reported an accuracy of 85%, Bernert et al. (46) reported 90% among 87 studies in their meta-analysis, and Barak-Corren et al. (47) reported 94%. The average accuracy across these studies is 89.2%. Assuming a gold standard accuracy of 100%, we calculated an effect size (Cohen's g) of 0.11 using the formula: g = (P—Po)/√[Po(1—Po)], where *P* is the expected accuracy (0.892) and Po is the gold standard accuracy (1.0).

For our power analysis, we set the following parameters: a two-tailed test, an alpha level of 0.05, a power of 0.80, and a constant proportion of 0.5 (representing a balanced dataset). The results indicated that a total sample size of 162 is required to detect an effect size of 0.11 with 80% power at a significance level of 0.05. The critical values for the lower and upper bounds of the acceptance region are 68 and 94, respectively. The actual power achieved with this sample size is 0.8046757, and the actual alpha level is 0.0491726.

In summary, to compare the accuracy of our models against the gold standard of a trained psychiatrist's evaluation with 80% power and a 5% significance level, we require a total sample size of *n* = 162, assuming an effect size of 0.11 based on the accuracies reported in previous comparable studies. As we expect a drop-out rate of 15%–20% due to technical issues, quality issues etc., we expect to collect *n* = 200 interviews.

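### The three cited accuracies average 89.7%, not 89.2%, so the stated 80% power at n = 162 does not follow from them

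*Protocol article*

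**What the plan says.** All of this is in the Sample size section of the protocol article. The effect size rests on three sources: the first "reported an accuracy of 85" per cent, the second "reported 90% among 87 studies in their meta-analysis", and the third gave 94%. The section then states "The average accuracy across these studies is 89.2" per cent. It goes on: "Assuming a gold standard accuracy of 100" per cent, "we calculated an effect size (Cohen's g) of 0.11 using the formula", with 0.892 as the expected accuracy and 1.0 as the reference. The test settings are "a two-tailed test, an alpha level of 0.05, a power of 0.80, and a constant proportion of 0.5". The result is that "a total sample size of 162 is required to detect an effect size of 0.11 with 80% power", with critical values 68 and 94. The section adds: "The actual power achieved with this sample size is 0.8046757, and the actual alpha level is 0.0491726". Allowing for 15%–20% loss, 200 interviews are to be collected.

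**The concern.** The average is the only route from the cited literature to the effect size, and it is wrong by about half a percentage point. The effect size is the small gap between the average and 100%, so half a point is a noticeable share of it: 0.108 becomes 0.103. The section presents n = 162 and 80% power as resting on accuracies from comparable studies. If the average is wrong, that link fails even on the section's own terms. The figure 0.892 would also be the natural starting value for anyone who redoes the calculation.

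**Working it through.** **Inputs (Sample size section).** Accuracies 85%, 90% and 94%; stated mean 89.2%; gold standard 100%; two-sided alpha 0.05; null proportion 0.5; n = 162; critical values 68 and 94.

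**1. Reproduce the printed result.** The printed figures match an exact binomial test of p = 0.5 with at most 0.025 in each tail, entering g = 1 − 0.892 = 0.108, rounded to 0.11, so that the alternative is p = 0.5 + 0.11 = 0.61.
- Rejection region at n = 162: X ≤ 68 or X ≥ 94.
- Alpha = P(X ≤ 68 | 0.5) + P(X ≥ 94 | 0.5) = 0.0491726, as printed.
- Power = P(X ≤ 68 | 0.61) + P(X ≥ 94 | 0.61) = 0.8046757, as printed.
- 162 is the smallest n at which power reaches 0.80, as printed.

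**2. Recompute the mean.** (85 + 90 + 94)/3 = 269/3 = 89.67%. The gap is 1 − 0.8967 = 0.1033, or 0.10 at two decimals.

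**3. Look for a reading that gives 89.2%.**
- Weighting the meta-analysis by its 87 studies: (85 + 87 × 90 + 94)/89 = 89.99%, which is further away. No weighting is stated.
- Rounded source values: the lowest values that round to the printed figures are 84.5, 89.5 and 93.5, with mean 89.17%. All three sources would have to lie almost at these limits.

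**4. Power in the same routine at n = 162** (the rejection region does not change).

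| Gap entered as g | Alternative | Power |
|---|---|---|
| 0.11 (stated mean, rounded) | 0.610 | 80.5% |
| 0.108 (stated mean, unrounded) | 0.608 | 79.0% |
| 0.1033 (correct mean, unrounded) | 0.6033 | 75.3% |
| 0.10 (correct mean, rounded) | 0.600 | 72.5% |

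Like for like, the averaging error costs 79.0 − 75.3 = 3.7 points unrounded, or 80.5 − 72.5 = 8.0 points with both values rounded. The difference 80.5 − 75.3 = 5.2 points mixes the two conventions: 80.5 − 79.0 = 1.5 points of it come from rounding 0.108 up to 0.11.

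**5. Smallest n reaching 80% in this routine.** 162 at g = 0.11; 171 at 0.108; 186 at 0.1033; 199 at 0.10. Exact power moves in a saw-tooth as n grows. At 0.1033 it stays at or above 80% only from n = 197.

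**6. After the stated loss.** 200 × 0.80 = 160 and 200 × 0.85 = 170 usable interviews. Over n = 160 to 170, power at g = 0.1033 runs from 71.0% to 75.9%. At the printed 0.11 the same range gives 76.7% to 81.1%, so not all of the shortfall from 80% comes from the average. To have 186 to 197 usable interviews, between 186/0.85 = 219 and 197/0.80 = 246 (rounded to whole interviews) would have to be collected.

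**The case against.** The strongest reply is that 75% is not the power of any comparison the article describes. The routine tests 0.61 against 0.5, whereas the text speaks of 0.892 against 1.0. The printed formula divides by √[1.0 × (1 − 1.0)] = 0, so it yields no effect size under either average. The direction of the change also depends on this routine, in which a more accurate model has a smaller g and needs a larger n. In a test of accuracy against a lower benchmark the correction would help. With assumed benchmarks (the article gives none), an exact two-sided test at n = 162 moves from 89.4% to 92.7% power against 0.80, and from 70.3% to 76.7% against 0.82. Finally, no binomial test against 0.5 appears under Outcomes or Statistical methods, so no planned analysis changes.

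All of this stands, and it limits the point. It does not remove it: the average is misstated in print, and the claim that 162 gives 80% power is explicitly based on it.

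A reader might infer two stronger things that the document does not support. One is that the averaging error by itself takes power from 80.5% to about 75%; part of that drop is the rounding to 0.11. The other is that the study's real power is 75%; the routine does not address the comparison of model with psychiatrist, so it supports neither 80% nor 75% for it.

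**Conclusion.** The point holds as an input error. The mean of the cited accuracies is 89.7% and the gap is 0.103. In the routine that matches every printed figure, power at n = 162 is 75.3% instead of 79.0% (unrounded), or 72.5% instead of 80.5% (both rounded). The stated 80% does not follow from the cited accuracies under either convention. This assumes that the three accuracies are as printed and that a simple mean was meant; the text gives no other weighting. The routine itself is inferred, but it agrees with the printed alpha and power to the last digit. Correcting the mean does not make the sample size valid. The undefined formula and the mismatch between the test and the stated comparison are the more basic faults and remain.

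**What to change.** In the Sample size section:
- Correct the average to 89.7% and the difference to 0.103, and use 0.897 as the expected accuracy in any revised calculation.
- Withdraw the statement that n = 162 gives 80% power.
- If the present routine is kept, give its result at n = 162 as about 75% (72% if 0.10 is entered). Say that 200 interviews with 15%–20% loss leave 160–170 usable and give about 71%–76% at 0.103, not 80%.
- State that this corrects an input only. The routine tests 0.61 against 0.5 and the formula is undefined at Po = 1.0, so the figure must not be presented as the power for comparing the model with the psychiatrist.

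The cost is wording and a less favourable stated power, with no change to recruitment or data collection. Holding to 80% within this routine would not be free: 186–197 usable interviews cannot come from 200 collected at the stated loss. Enlarging the study on the strength of this routine is not recommended, because it does not test the stated comparison.

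### The effect-size formula is undefined at its stated inputs, and the printed 80% power for n = 162 belongs to 61% versus 50% accuracy, not to the comparison with the gold standard

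*Protocol article*

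**What the plan says.** All of the following is in the Sample size section of the protocol article.

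- The aim is "comparing the accuracy of our models against the gold standard of a trained psychiatrist's evaluation".
- Three earlier reports are cited with accuracies of 85%, 90% and 94%, followed by "The average accuracy across these studies is 89.2"%.
- The effect size: "Assuming a gold standard accuracy of 100%, we calculated an effect size (Cohen's g) of 0.11 using the formula". The expression that follows divides the difference between P and Po by √[Po(1 − Po)]. P is set to 0.892, and the text adds that "Po is the gold standard accuracy (1.0").
- The software settings: "a two-tailed test, an alpha level of 0.05, a power of 0.80, and a constant proportion of 0.5 (representing a balanced dataset").
- The result: "a total sample size of 162 is required to detect an effect size of 0.11 with 80% power at a significance level of 0.05".
- Software output reported with it: limits of 68 and 94 for the test, actual power 0.8046757 and actual alpha 0.0491726.
- The section concludes that 162 gives 80% power for the comparison with the trained psychiatrist, and plans 200 interviews to allow for 15–20% loss.

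**The concern.** Two steps do not fit together. The effect size is defined as a distance from a benchmark of 100%, but the test is run around a benchmark of 50%. The formula meant to link the two cannot be evaluated at the stated benchmark. If the printed power belongs to a different hypothesis, the protocol's only sample-size justification does not support the sentence that concludes it, although outputs given to seven decimals invite the reader to trust it.

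The value 0.5 is also described as a property of the data set. In a one-sample proportion test it is the null value. It equals the accuracy of an uninformative classifier only if the two suicidality classes are equally frequent. Patients enter by ICD-10 diagnosis (Eligibility criteria), and nothing in the design balances suicidality.

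**Working it through.** **Inputs (Sample size section).** P = 0.892; Po = 1.0; g = 0.11; constant proportion 0.5; two-tailed; alpha 0.05; power 0.80; n = 162; critical values 68 and 94.

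**Step 1: the formula as printed.** (0.892 − 1.0)/√[1.0 × (1 − 1.0)] = −0.108/0, which is undefined. The raw difference is |0.892 − 1.0| = 0.108, which rounds to 0.11.

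**Step 2: reproducing the plan's own figures.** In a one-sample proportion test, Cohen's g is the distance from the null proportion. With g = 0.11 and null 0.5, the alternative is 0.5 + 0.11 = 0.61 (by symmetry also 0.39). Exact binomial, reject if X ≤ 68 or X ≥ 94, n = 162:

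| Quantity | Recomputed | Printed |
|---|---|---|
| Alpha: P(reject) at p = 0.50 | 0.04917259 | 0.0491726 |
| Power: P(reject) at p = 0.61 | 0.80467569 | 0.8046757 |
| First n with power ≥ 0.80 | 162 (160: 0.796; 161: 0.777) | 162 |

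The software calculation is correct for 61% versus 50%, and it is that hypothesis which the printed 80% describes.

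**Step 3: the hypotheses the text describes.**

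- Accuracy 0.892 against the null actually used, 0.5: g = 0.892 − 0.5 = 0.392. Power at n = 162 is about 1.00; n = 12 already gives 0.868.
- Accuracy 0.892 against Po = 1.0: the null has no variance and one error rejects it. P(at least one error in 162) = 1 − 0.892^162 > 0.9999; n = 15 reaches 80%.

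Neither gives n = 162 at 80%.

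**Step 4: link to the planned analyses.** Outcomes names intraclass correlations or t-tests. The Statistical methods section names mixed-effects logistic and linear regression, a mixed-effects ANOVA, and a late-fusion comparison on AUC, sensitivity and specificity. None is a one-sample test of accuracy against 0.5.

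**Step 5: the average.** (85 + 90 + 94)/3 = 89.67%, against 89.2% as stated.

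**Step 6: precision at n = 162.** Half-width of a 95% interval for accuracy 0.892 with independent interviews: 1.96 × √(0.892 × 0.108/162) = 0.048. The Participant timeline allows up to five sessions per patient. As an illustration only, with five per patient and an assumed intraclass correlation of 0.3 to 0.5 (not in the document), the design effect is 1 + 4 × 0.3 = 2.2 to 1 + 4 × 0.5 = 3.0, and the half-width becomes 0.048 × √2.2 = 0.071 to 0.048 × √3.0 = 0.083.

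**The case against.** **The study is exploratory and the number may be adequate.** There is no comparator, Outcomes calls the clinician–model comparison an initial exploratory analysis, and 0.892 against 0.50 would be heavily over-powered. This stands: nothing here shows that 162 is too small. It does not rescue the sentence that assigns 80% power to a comparison the calculation never addressed.

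**A reader might infer that a model could be declared successful at 94/162 (58.0%), which a rule always answering not suicidal would usually beat.** The documents do not support this. They set no success rule at 94; the critical values are reported software output. The claim also depends on an unstated prevalence. At an assumed 20–35% suicidal, such a rule scores 65–80% and reaches 94 with probability 0.97 or more. At 40% the probability is 0.72, at 45% 0.24, and at 49% about 0.05. The only prevalence derivable from the article comes from the admission-note study in the Discussion (accuracy 87.5%, sensitivity 83.0%, specificity 91.8%): (91.8 − 87.5)/(91.8 − 83.0) = 0.49. That is a different text type, so it does not settle the prevalence here, but it is close to balance. What remains is that balance is assumed, not ensured.

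**The plan does not rely on raw accuracy.** Correct: sensitivity, specificity, predictive values and AUC are already planned.

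**A reader might infer that 89.2% and 100% play no part, or that 89.2% should simply become 89.7%.** Both figures do enter, through their difference; they are misapplied. The cited accuracies may be rounded or weighted (84.5, 89.5 and 93.5 average 89.17), so the text shows a mismatch to explain, not a known correct value.

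**Conclusion.** The point holds on the Sample size section alone. The formula has no value at Po = 1.0, and the printed alpha and power match 61% (or 39%) versus 50% to every digit. The statement that 162 gives 80% power to compare model accuracy with the psychiatrist gold standard is wrong as written, and no analysis described in the article is the test that was powered. These conclusions need no outside assumption; only the prevalence and clustering figures above do.

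The size of the error is a change of hypothesis: about 80% power for a true accuracy of 61% against 50%, about 100% for 89.2% against 50%, and no usable power statement against 100%. The binomial calculation also treats interviews as independent. None of this implies a change in enrolment.

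**What to change.** 1. Delete the effect-size formula and the claim of 80% power for the gold-standard comparison.
2. Replace them with one of two statements: (a) that 162 independent interviews give 80% power to distinguish 61% from 50% accuracy; or (b) the expected precision for accuracy, sensitivity and specificity at n = 162, with the class split assumed and an allowance for up to five sessions per patient. The ±4.8 points for accuracy is the independent-interview value and should be labelled as such.
3. Describe 0.5 as the null proportion, not as a balanced data set, and report observed accuracy next to the observed majority-class rate.
4. Reconcile the 89.2% average with the printed 85%, 90% and 94%, stating any weighting or unrounded inputs.

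The cost is rewriting one section, with no change to enrolment. The stated justification becomes more modest than the present one.

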What accuracy should be expected from an AI-based suicide evaluation? Large language models demonstrate strong performance in detecting depression and suicide risk from clinical narratives, with recent real-world validation substantially informing expectations for psychotherapy transcripts. In a recent cross-sectional study of 100 admission notes from a psychiatric hospital, a German-fine-tuned Llama-2 model achieved 87.5% accuracy, 83.0% sensitivity, and 91.8% specificity in identifying suicidality status against expert ground truth, demonstrating robust performance across varied prompting strategies while preserving data privacy (64). To contextualize these capabilities, human interrater reliability in assessing mental health from dialogue provides an essential benchmark. Unstructured suicide risk assessment shows substantially lower concordance: psychotherapists demonstrate Gwet's AC₁ = 0.44 with only 58% identical risk classifications, while psychology students achieve AC₁ = 0.35 (65). Unstructured psychiatric diagnosis using clinical interviews yields *κ* = 0.24–0.43 (fair at best), compared to *κ* = 0.75 (substantial) when structured protocols guide assessment (66). This empirical gap is instructive: current clinical practice relies on unstructured judgment with relatively poor reliability, particularly for suicide risk estimation. Consequently, LLM-assisted assessment of suicidality in psychotherapy transcripts is already useful potentially when achieving only modest accuracy performance.

The dialogic nature of therapy sessions introduces complexities in transcription and analysis. Colloquialisms, pauses, overlapping speech, and non-verbal cues are integral to therapeutic communication but challenging to capture and analyze (67). Our multimodal approach aims to address these challenges by incorporating advanced speech recognition and sentiment analysis techniques. However, the nuances of therapeutic dialogue may still pose difficulties in accurate interpretation, necessitating ongoing refinement of our multimodal models.

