The SPEAK-SAFE study utilizes both structured (questionnaires) and unstructured (conversation recordings) data. While structured data offers standardized, easily quantifiable information, unstructured data provides rich, contextual insights into patient-therapist interactions (68). Our decision to focus on conversational data stems from its potential to capture subtle linguistic markers of mental health states that may not be evident in structured assessments. Our aim is to predict occurring changes in the structured data, what we consider as ground truth, by using the rich, unstructured speech data.

A limitation of the current study design is the lack of long-term follow-up to assess the predictive accuracy of the NLP/multimodal model over time. This has been done so far by only few studies (36). While our approach provides valuable insights into immediate risk assessment, the dynamic nature of mental health conditions necessitates longitudinal evaluation. Future research should incorporate extended follow-up periods to validate the model's long-term predictive capabilities and assess its utility in tracking treatment progress.

The use of AI in mental healthcare raises important ethical considerations. Potential biases in NLP/multimodal models, particularly regarding cultural and linguistic diversity, must be carefully addressed (69). Moreover, the integration of AI-based tools in clinical decision-making necessitates a balance between technological assistance and human clinical judgment. Our study emphasizes the importance of human oversight in interpreting AI-generated insights, recognizing that these tools should augment rather than replace clinical expertise.

The SPEAK-SAFE study has significant potential to enhance mental health care. By providing clinicians with AI-assisted risk assessment tools, we aim to improve the accuracy and efficiency of suicide risk evaluation (34). This could lead to more timely interventions and personalized treatment strategies. However, the successful integration of such tools into clinical workflows requires careful consideration of user acceptance, training needs, and potential impacts on the therapeutic relationship.

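### The sample-size section claims 80% power to compare model accuracy with the psychiatrist gold standard, but its figures are those of a test of 61% against 50% correct, which can show only better-than-chance performance

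*Protocol article*

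**What the plan says.** The Sample size section of the protocol article presents the calculation as a comparison of model accuracy with a trained psychiatrist's evaluation. It averages three published accuracies (85%, 90% and 94%) to 89.2%, takes the gold standard as 100% accurate, and reports an effect size of 0.11 from a formula in those two values.

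The settings entered are "a two-tailed test, an alpha level of 0.05, a power of 0.80" and "a constant proportion of 0.5 (representing a balanced dataset"). The result is that "a total sample size of 162 is required to detect an effect size of 0.11 with 80% power". The section adds: "The critical values for the lower and upper bounds of the acceptance region are 68 and 94, respectively", and "The actual power achieved with this sample size is 0.8046757, and the actual alpha level is 0.0491726". Its closing summary repeats that 162 is the number needed to compare the models with the gold standard. Allowing for 15%–20% loss, 200 interviews are to be collected.

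The Discussion says that "human interrater reliability in assessing mental health from dialogue provides an essential benchmark". For psychotherapists' unstructured suicide-risk assessment it reports a Gwet's AC1 of 0.44 "with only 58% identical risk classifications". It later says "we aim to improve the accuracy and efficiency of suicide risk evaluation".

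**The concern.** The section describes one comparison and calculates another. The stated purpose is to set the model against a gold standard assumed to be 100% accurate, but the test that yields 162 has 50% as its null value. A reader who takes the 80% power at face value would think the study is sized to judge closeness to expert assessment. It is sized only to tell a model from a coin.

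This matters because the Discussion goes further and speaks of improving the accuracy of risk evaluation. A significant result against 50% could be cited for that claim without supporting it. Separately, the average behind the effect size does not follow from the three figures printed beside it, so the power for 162 is also affected.

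**Working it through.** **Inputs, all from the Sample size section unless noted.** n = 162; null 0.5; g = 0.11; two-sided alpha 0.05; critical values 68 and 94; cited accuracies 85%, 90% and 94%; gold standard 1.0. From the Discussion: 58% identical classifications and AC1 = 0.44.

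**1. Reproducing the plan's figures.** Let X be the number correct, X ~ Binomial(162, p), and reject if X ≤ 68 or X ≥ 94.
- At p = 0.50 the rejection probability is 0.0491726, equal to the stated alpha.
- At p = 0.50 + 0.11 = 0.61 it is 0.8046757, equal to the stated power.
- 162 is the smallest n with exact power of at least 0.80.

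The text calls 68 and 94 bounds of the acceptance region. Read literally (reject at ≤ 67 or ≥ 95), alpha would be 0.0336 and power 0.758, which contradicts the stated values. The rule above is therefore the one that was run. The null is 50% and the powered alternative is 61%.

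**2. Where 0.11 comes from.** The printed formula is g = (P − P0)/√[P0(1 − P0)]. With P0 = 1.0 the denominator is √(1.0 × 0) = 0, so it cannot give 0.11. The value does match the plain gap 1.0 − 0.892 = 0.108, rounded up. That gap below 100% was then used as a distance above 50%. The gold standard and the expected 89.2% enter the calculation only through this step; neither is a hypothesis in the test.

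**3. What the threshold means.** The upper critical value is 94/162 = 58.0% correct. A model that just reaches it differs significantly from 50% and may still be far from the reference.

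**4. The averaging error.** (85 + 90 + 94)/3 = 269/3 = 89.7%, not 89.2%. Following the plan's own method:
- g = 1 − 0.897 = 0.103, so the alternative is 0.603.
- Exact power at n = 162 with limits 68 and 94 is 0.750.
- The smallest n with power of at least 0.80 is 186 (critical values 79 and 107, power 0.802).

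The direction is itself telling: a more accurate expected model needs a larger sample, because the gap from 100% has been used as a gap from 50%.

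**5. Why 58% agreement is not a ready null.** If observed agreement is 0.58 and AC1 is 0.44, chance agreement is (0.58 − 0.44)/(1 − 0.44) = 0.25. A balanced binary accuracy has chance level 0.50. The two percentages are on different scales. If 0.58 were nevertheless used as the null at n = 162, the upper critical value would be 107/162 = 66.0%. Power at the plan's powered alternative of 61% would fall from 80% to 11%, although it would exceed 99.9% at 89.2%.

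**The case against.** The strongest defence is that the binomial test appears only in the Sample size section. The Outcomes section names intraclass correlations or t-tests in an initial exploratory analysis. The Statistical methods section names mixed models, sensitivity, specificity, predictive values and AUC. Nowhere is 94/162 made a criterion for success, and a better-than-chance null is a defensible basis for sizing an exploratory study. All of this stands. It means that 50% need not be abandoned. It does not rescue the section's description of what the 80% power is for.

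A reader might go further and infer that, because 58.0% coincides with the 58% human figure, a model no better than clinicians would pass about half the time. The arithmetic is right: at a true rate of 58%, P(X ≥ 94) = 0.531. The documents do not support the conclusion. The 58% is agreement between raters on risk classes, not accuracy against a reference, and there is no pass rule. The coincidence illustrates how low the threshold is and no more. For the same reason, replacing 0.5 by 0.58 is not a correction that the protocol's own figures dictate.

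On the mean, the cited accuracies may have been rounded. If each were half a point lower, the mean would be (84.5 + 89.5 + 93.5)/3 = 89.2%, so 89.2% needs all three to sit at the rounding limit. As printed, the figures do not give it.

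**Conclusion.** The point holds in this form: the 80% power belongs to a test of 61% against 50% correct, and the Sample size section misdescribes it as power for a comparison with the gold standard. The reproduction of alpha and power to seven decimals leaves little room for another reading. Rejecting 50% would support a claim of better-than-chance performance only, not parity with the gold standard and not improvement on clinical judgement.

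The arithmetic slip is smaller but real. With the mean at 89.7%, the plan's method gives about 75% power at 162 instead of 80%, and 186 for 80%. These figures take g as 0.103 without further rounding. They assume, as the plan does, independent interviews, and they keep the plan's construction of the effect size, which step 2 shows has no sound derivation. They show what the plan's own method yields and do not endorse that method.

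**What to change.** In the Sample size section:

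1. State that the 80% power is for 61% versus 50% agreement with the psychiatrist reference, and that rejecting 50% shows only better-than-chance performance. Reword the opening and closing sentences, which describe a comparison with the gold standard.
2. Correct the mean of the three cited accuracies to 89.7% and restate the effect size and power: under the plan's method 0.103, about 75% at 162, and 186 for 80%. Remove or replace the formula, which is undefined at P0 = 1.0.
3. If a claim relative to clinicians is intended, state and justify a comparator value on the accuracy scale and report power at n = 162 for that null. The 58% agreement figure should not be adopted for this without justification. If no such claim is intended, say that this test does not support the Discussion's aim of improving accuracy.

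The first and third items cost wording and at most one recalculation. For the second, the sponsor can accept about 75% power or keep 80% by collecting more. With 15%–20% loss, 200 interviews leave 170 to 160 analysable, whereas 186 analysable would need 186/0.85 = 219 to 186/0.80 = 233.
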